### Randomization, Blinding, and Treatment Allocation

Participants will be randomized after completing baseline assessments. Assignment to the training program will be by an unblinded Senior Research Professional. The study statistician will use a computer-generated randomization list for the study. Block randomization with block sizes of 2, 4, and 6 will be used to randomize participants into two groups (high- vs. low-resistance IMST) in a 1:1 ratio. Randomization will be stratified by sex (M/F) and OSA disease severity (moderate/severe). The randomization list will be stored in a .CSV file with the randomized group assignment hidden and only revealed by the Senior Research Professional at the time of randomization. Assignment to groups will be sequentially within strata.

Randomization will, on average, balance CPAP users (Yes/No) between the two arms within sex and severity strata however, the effect of treatment may differ depending on CPAP use. We will account for the potential effect of CPAP on outcomes, and possible interaction with treatment, by including CPAP and treatment-by-CPAP interaction effects in the mixed effects models. Based our pilot trials, we anticipate ~10–15% CPAP users in our study sample. The power to detect either a CPAP or a treatment-by-CPAP interaction, that is, our ability to tease out CPAP from IMST effects, will depend on the treatment-by-CPAP cell sample sizes and effect sizes.

Outcomes assessors and data analysts will be blinded to training group allocation. As both training programs have the potential to affect outcome measures, neither is considered a “placebo.” Subjects will be blinded to their allocation group.

### Study Withdrawal

Participants can withdraw consent at any time and for any reason if they wish to do so without harm of penalty. The researcher also may remove the participant from the study at any time if they believe study procedures have not been followed, for the benefit of the participant, or in the event of an adverse event (i.e., the development of severe side effects that, in the opinion of the supervising physicians, make it unsafe for the subject to continue in the study). Other discontinuation criteria will include cardiovascular or metabolic disease-related events (e.g., hypertensive crisis, myocardial ischemia/angina, myocardial infarction), major surgery, or other serious changes in physical or mental health status. The reason/s for withdrawal will be registered in the electronic Case Report Form.

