### Statistical Analysis

The same statistical approach will be used to address all hypotheses, as each hypothesis uses data collected on continuous outcomes (e.g., casual and 24-h BP) from a two-arm design with multiple time points. A standard repeated measures (with the number of time points depending on outcome) mixed model analysis of variance will be used to estimate average change from baseline within arms. Models will adjust for stratification on OSA severity, sex, and age. Subject specific random effects will be used to account for the repeated measures on an individual. Inferences will be based on available data using maximum likelihood, which accommodates data missing at random. We propose a within-individual analysis for the study (comparisons between arms will be based on average change from baseline vs. average at endpoint) as the correlations between baseline and 6-week SBP and plasma norepinephrine in our preliminary data were ~0.60 or larger (49). Effect sizes and confidence intervals will be reported in addition to *p*-values. Unless otherwise mentioned, tests will be two-sided and conducted at the 5% significance level.

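### The withdrawal rule lets a randomised participant be removed from the study for not following procedures, without keeping outcome assessment going, so avoidable adherence-related missing data may arise that the stated analysis need not correct

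*Protocol article*

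**What the plan says.** The Study Withdrawal section gives the research team a discretionary power after randomisation: "The researcher also may remove the participant from the study at any time if they believe study procedures have not been followed". It sets no threshold for what counts as not following procedures. It then adds clinical grounds: "Other discontinuation criteria will include cardiovascular or metabolic disease-related events (e.g., hypertensive crisis, myocardial ischemia/angina, myocardial infarction", and others. It closes with a record-keeping step: "The reason/s for withdrawal will be registered in the electronic Case Report Form". The section does not distinguish stopping training from stopping outcome assessment.

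The Statistical Analysis section states how incomplete data are handled: "Inferences will be based on available data using maximum likelihood, which accommodates data missing at random". On covariates it says: "Models will adjust for stratification on OSA severity, sex, and age". The randomisation section adds two further terms by "including CPAP and treatment-by-CPAP interaction effects in the mixed effects models". Adherence appears in neither list.

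Three other places bear on the point. The Adherence section defines success as at least 70% of sessions and attaches no consequence to falling short. The Discussion names the degree of home adherence as one of four things the study will determine. The Follow-Up Evaluations section speaks of reassessing all participants, but describes people who have already completed the post-intervention assessments.

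**The concern.** The rule acts after randomisation, rests on a belief, and takes the person out of the study. Poor adherence to training is an obvious situation in which it might be used. People who train little can be expected to gain little, so removing them selectively deletes the small responses in the high-resistance arm. A likelihood analysis under missing at random then predicts the missing outcomes from participants in the same arm with similar observed data, who are mostly adherers. The estimate moves from the effect of being assigned to high-resistance training towards the effect in those who comply.

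The rule could also affect the adherence result. If those removed leave the denominator, home adherence looks better than it was.

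**Working it through.** **The plan's own figures.** Sample Size Calculation and Power claims over 80% power with 45 completers per arm at an effect size of 0.63; "tests will be two-sided and conducted at the 5% significance level". A two-sample t calculation gives 84.0% (normal approximation 84.8%), so the claim reproduces and is not in dispute. The same section assumes 75% completion in its remark on female participants. Applied to the whole sample, 122 × 0.75 = 91.5 completers, or about 45 per arm. Up to about a quarter of final outcomes could therefore be missing for all reasons together.

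**What the model can use.** The listed terms are OSA severity, sex, age, CPAP and treatment-by-CPAP. None carries adherence. Interim SBP could carry some of it, because people who do not train would show less mid-study fall. Whether interim SBP enters the model is unclear:
- The casual SBP outcome section says weekly recording, and the analysis section lets the number of time points vary by outcome.
- Study Design names four assessment time points, and supervised visits become twice monthly from week 4.
- The schedule's casual BP row covers only the baseline, post and follow-up visits.
- 24-h SBP and norepinephrine have no measurements during training. Anyone removed then contributes baseline only.

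**Removal for non-adherence.** Assumptions, none of them from the documents: 25% of each arm non-adherent; benefit D = 10 mmHg in high-resistance adherers, zero in non-adherers and in the sham arm; a fraction r of non-adherers removed before the post-intervention visit, in both arms.

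True all-randomised effect = 0.75 × D = 7.5 mmHg.

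If only baseline informs the missing outcomes and adherence is unrelated to baseline, the estimate = D × 0.75 / (1 − 0.25r):
- r = 0.2 (5% of the arm removed): 10 × 0.75/0.95 = 7.9, overstated by 0.4
- r = 0.5 (12.5% removed): 10 × 0.75/0.875 = 8.6, overstated by 1.1
- r = 1 (25% removed): 10 × 0.75/0.75 = 10.0, overstated by 2.5

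A simulation with 1,000,000 per arm gave the same baseline-only values (7.89, 8.58, 10.00). It assumed SD 12 mmHg, correlation 0.6 with baseline (the plan reports about 0.60 or larger), correlation 0.7 between mid-study and post values, and 60% of the benefit present mid-study. With mid-study SBP also in the model, the estimates were 7.75, 8.21 and 9.19. The overstatement was then about 0.3, 0.7 and 1.7 mmHg, so interim SBP reduces the bias without removing it.

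The bias is proportional to D. The Discussion cites reductions of 6–12 mmHg. The baseline-only overstatement is D × [0.75/(1 − 0.25r) − 0.75]. For D = 6 it runs from 0.2 (r = 0.2) to 1.5 (r = 1); for D = 12, from 0.5 to 3.0.

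**Effect on the adherence result.** With the same inputs, if removed people are left out, the apparent share of adherers rises from 75% to 0.75/0.95 = 79%, 0.75/0.875 = 86%, or 100%.

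**Removal after a BP event.** The same simulation removed 50% or 100% of those with SBP above 150 mmHg, against a true difference of about 7.5:
- Trigger is the recorded mid-study SBP, and that reading is in the model: 7.5, no bias.
- Same trigger, reading left out: 7.4 to 7.2.
- Trigger is an unrecorded SBP at the post-intervention time: 7.2 to 6.8 with mid-study SBP in the model, 7.1 to 6.6 without.

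Where bias arises here, it is towards no effect.

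**The case against.** The rule is permissive and does not name missed training sessions. Falling below 70% adherence is only a classification, and a study that wants to measure home adherence has reason not to expel poor adherers. This stands: the documents allow the practice but do not prescribe it, so the bias is conditional on use.

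A reader might infer that the rule defeats the missing-at-random analysis. The documents do not support that. Missing at random permits dependence on observed BP, so removal after a recorded high reading that is in the model causes no bias. Sessions are logged by the device and withdrawal reasons are recorded, so dependence on adherence can be examined. Those records cannot, however, restore BP values never measured.

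A reader might also infer that the unblinded technician decides who is removed. The text assigns the decision to the researcher. It neither gives it to the technician nor confines it to blinded staff.

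Finally, the analysis set, sensitivity analyses and fuller follow-up rules may sit in the SAP or full protocol. Their absence from the article is not counted here. What remains is the rule as stated: removal is from the study, on belief, with training and outcome assessment not separated.

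**Conclusion.** The point holds in limited form. As written, the withdrawal rule can create avoidable missing outcomes that depend on adherence, and the listed model terms need not correct for it. The direction is towards overstating the benefit. The size is about 0.3 to 2.5 mmHg with 25% non-adherence and a 10 mmHg benefit confined to adherers. The low end needs one fifth of non-adherers removed and mid-study SBP in the model; the high end needs all of them removed and baseline only.

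It would be tempting to treat the whole 25% non-completion as removals for non-adherence, or to say that randomisation no longer protects the primary comparison. Neither follows. The 25% covers loss for any reason, and the number who would be removed under this rule is unknown. The BP-event grounds are a lesser concern, for the reason shown above. This is a cheap improvement to the plan, not evidence that the primary result will be invalid.

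**What to change.** In Study Withdrawal, state that not following study procedures may end training but does not end outcome assessment. Add that every randomised participant who stops training for any reason and has not withdrawn consent is still invited, where safe, to the already scheduled post-intervention, 4-week and 12-week BP assessments, and is analysed as randomised. Leave the clinical discontinuation criteria as they are.

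The cost is a sentence or two of protocol wording and a few planned visits kept rather than dropped. The estimated effect may come out somewhat smaller, because people who trained little would then be counted.

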### Adverse Events

An adverse event (AE) is any harmful and unintended reaction to a study assessment or intervention under investigation. Participants will be instructed to report side effects and AEs to members of the study team. All AEs occurring after the informed consent is signed and up until the subject has completed the study will be reported to the study physicians.

A serious adverse event (SAE) is any untoward medical occurrence that results in death, is life-threatening, requires inpatient hospitalization, results in persistent or significant disability/incapacity. In the event an SAE occurs, it will be reported to the University of Arizona IRB and the supervising physician within a maximum of 24 h from the moment the event is identified.

Throughout the study, the Principal Investigator will prepare yearly safety reports to the regulatory authorities and to the IRB at The University of Arizona following the schedule established in the current institutional guidelines.

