### Intervention

Following baseline assessments, participants will begin the training intervention. All training will be performed on the POWERbreathe™ K3 trainer (POWERbreathe™ K3, POWERbreathe International Ltd., Warwickshire, ENG), a handheld pressure-threshold device that can: (1) be pre-programmed to provide the appropriate resistance to inspiration, and (2) record data from all training sessions. Each participant will be provided their own device on which to perform their prescribed exercise at home, 5 days/week for 24 weeks, and will receive verbal and written instruction on the training protocol and K3 operation from the unblinded Research Technician.

The Research Technician will supervise the subject's first training session to ensure proper technique and comprehension. In training weeks 1–3, participants will perform 5 training sessions per week; one training session will be supervised by the Research Technician in the CATS facility, and 4 training sessions will be performed unsupervised at home. In training weeks 4–24, participants will perform training sessions unsupervised at home returning to the CATS facility for supervised training sessions twice monthly. At each visit, the unblinded Research Technician will determine the participant's casual BP, collect sleep and activity logs, transfer saved training data from the K3 device, and record any changes in medications, diet, exercise, and/or health status since the previous visit. The participant will complete 3 PI_max_ efforts to establish the following weeks' training level. The new resistance will be set on the K3 using the *Manual* function to ensure that the target resistance remains the same until the next in-person visit. The participant then will perform one supervised training session at this new training level. Subjects will be contacted weekly *via* phone or email to encourage participants and aid in retention and adherence.

Subjects assigned to high-resistance IMST will train against a resistance set at 75% of their PI_max_. Subjects randomly assigned to low-resistance IMST will train against a resistance set at 15% of PI_max_. Subjects in both groups will perform 5 sets of 6 breaths, with 1 min rest between sets, for a total of 30 breaths per day (49). All exercise sessions will be recorded in the device memory card and participants will be required to complete a weekly training log.

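### The AE definition requires causation, while the SAE definition does not; non-serious events judged unrelated fall outside AE reporting, and an SAE need not be an AE

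*Protocol article*

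**What the plan says.** The section Adverse Events of the protocol article defines the term: "An adverse event (AE) is any harmful and unintended reaction to a study assessment or intervention under investigation". It then says who reports, "Participants will be instructed to report side effects and AEs to members of the study team", and where the reports go: "All AEs occurring after the informed consent is signed and up until the subject has completed the study will be reported to the study physicians".

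The next paragraph of that section defines the serious event: "A serious adverse event (SAE) is any untoward medical occurrence that results in death, is life-threatening, requires inpatient hospitalization", with lasting or significant disability as the remaining criterion. The reporting rule for these events is separate: "In the event an SAE occurs, it will be reported to the University of Arizona IRB and the supervising physician within a maximum of 24" hours of its being identified.

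Study Withdrawal names an adverse event as one ground for removing a participant. It explains the term in brackets as severe side effects that, in the physicians' view, make it unsafe to go on. Cardiovascular and metabolic events, major surgery and other serious changes in health are listed apart from this, as other criteria. Reasons for withdrawal go into the electronic case report form.

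Intervention describes the in-person training visits: "At each visit, the unblinded Research Technician will determine the participant's casual BP, collect sleep and activity logs". The same sentence has the technician "record any changes in medications, diet, exercise, and/or health status since the previous visit".

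**The concern.** An AE definition usually decides only whether something untoward happened. Whether the study caused it is a separate judgement, made afterwards and recorded beside the event. Here the causal judgement sits inside the definition. A participant or staff member has to regard an event as a reaction before the AE reporting rule applies to it.

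Two things follow. First, the document does not agree with itself on what an AE is, and its SAEs are not a subset of its AEs. Second, a non-serious event such as a dizzy spell, a fall or palpitations that is put down to something else need not reach the study physicians as an AE. Whatever AE counts are eventually reported would then mix how often events happened with how often someone attributed them to the study.

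**Working it through.** No arithmetic decides this point, so the definitions are set side by side and each kind of event is followed through the rules as written.

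**Three meanings**
- Adverse Events, AE: harmful, unintended and a reaction to an assessment or the intervention. Causation required; no severity threshold.
- Adverse Events, SAE: an untoward occurrence that meets a seriousness criterion. No causation required.
- Study Withdrawal, AE: side effects of a severe kind. Causation required, and severity required as well.

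**Following events through**

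| Event | AE as defined? | SAE as defined? | Route described in the article |
|---|---|---|---|
| Non-serious, judged a reaction | yes | no | AE report to study physicians |
| Non-serious, judged unrelated | no | no | no AE report; may be noted as a health change at a training visit, or in the case report form if it leads to withdrawal |
| Serious, judged a reaction | yes | yes | both reporting rules |
| Serious, judged unrelated | no | yes | IRB and supervising physician within 24 hours |

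The fourth row shows that an SAE need not be an AE. A hospitalisation after a road accident is an example. The second row is the gap: neither reporting rule reaches the event. Under the Study Withdrawal gloss, read as a definition, even a mild event judged a reaction (first row) would not be an AE.

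**How far the other routes reach**
The health-change record belongs to the in-person training visits, which are weekly in weeks 1–3 and twice monthly in weeks 4–24. The article does not describe it as AE capture. Follow-Up Evaluations describes weekly phone or email contact during free living and does not say that health changes are recorded then. Free living to the last follow-up is about 12 weeks of roughly 42 weeks per participant, so 12/42 ≈ 0.29 of participation lies outside the training-visit route. The withdrawal route covers only events that end participation.

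**When relatedness is judged**
Participants are told to report side effects and AEs, and as the article uses them both terms imply a cause. The judgement therefore comes before the report. The arms train at 75% and 15% of maximal inspiratory pressure, so participants could differ by arm in how readily they call a symptom a reaction, even if they do not know their allocation. That is a plausible mechanism; the document has no data that would show it.

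**The case against.** The strongest reply is that little is lost. SAEs carry no relatedness condition, so unrelated serious events are reported promptly. Health changes of any cause are noted at training visits, and reasons for withdrawal are entered. The SAE rule stands on its own, so nothing goes unreported merely because an SAE is not also an AE. The bracketed gloss in Study Withdrawal may be meant only to say which AEs lead to removal. The text is also a condensed article: the AE log and its relatedness field may well exist in the full protocol.

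Much of this stands, and it limits the point. A reader might infer more than the documents support:
- *That events judged unrelated are never recorded.* They can be, by the three routes just named.
- *That the unblinded technician makes the causal call.* The article has the technician record any change in health status, which is unfiltered. It does not say who judges relatedness.
- *That a planned between-arm safety comparison is biased.* Statistical Analysis covers continuous outcomes, and no comparison of AE counts is stated.
- *That the Safety Officer sees only events passing the causal condition.* Data Monitoring refers to safety data in general, without that limit.
- *That a given percentage of events is lost.* The article has no event rates and no split by relatedness.

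What the reply does not remove is the second row of the table. The causal definition is stated text, not a detail left out for brevity, and followed literally it keeps non-serious events judged unrelated out of AE reporting to the study physicians.

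**Conclusion.** The point holds in limited form. The AE and SAE definitions in Adverse Events and the gloss in Study Withdrawal are inconsistent. As written, non-serious events judged unrelated are outside AE reporting, although some will be noted elsewhere. The number affected cannot be worked out from the document; the exposed group is 92 to 122 participants over about 42 weeks each. The attribution bias in any AE counts is a risk created by the order of steps, not a shown effect. No stated efficacy estimate or test changes.

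The conclusion assumes that staff follow the published wording. If the full protocol already defines an AE without causation, only the article's wording is at fault and should be brought into line.

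**What to change.** In Adverse Events, define an AE as any untoward medical occurrence from consent to study completion, whether or not it is considered related to an assessment or the intervention. Record relatedness as a separate field. Define an SAE as an AE that meets a seriousness criterion. Reconcile the use of the term in Study Withdrawal with this definition; this is a wording change and need not alter the criteria for discontinuation.

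The cost is a short amendment and a slightly longer AE log.

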### Statistical Analysis

The same statistical approach will be used to address all hypotheses, as each hypothesis uses data collected on continuous outcomes (e.g., casual and 24-h BP) from a two-arm design with multiple time points. A standard repeated measures (with the number of time points depending on outcome) mixed model analysis of variance will be used to estimate average change from baseline within arms. Models will adjust for stratification on OSA severity, sex, and age. Subject specific random effects will be used to account for the repeated measures on an individual. Inferences will be based on available data using maximum likelihood, which accommodates data missing at random. We propose a within-individual analysis for the study (comparisons between arms will be based on average change from baseline vs. average at endpoint) as the correlations between baseline and 6-week SBP and plasma norepinephrine in our preliminary data were ~0.60 or larger (49). Effect sizes and confidence intervals will be reported in addition to *p*-values. Unless otherwise mentioned, tests will be two-sided and conducted at the 5% significance level.

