### Outcomes

#### Primary Outcome

##### Casual Systolic Blood Pressure

Casual SBP will be assessed in accordance with ACC/AHA guidelines (28) between 7 and 10 a.m. and after overnight fasting. Subjects will be seated quietly with their back supported, feet flat on the floor, and arms supported on a table at heart level with the palms facing up. SBP will be measured with an automated oscillometric sphygmomanometer (SunTech CT40, SunTech Medical), validated according to standards set by the British Hypertension Society, International Protocol and Association for the Advancement of Medical Instrumentation (53), and calibrated regularly by the manufacturer. Measurements will be performed in triplicate over the brachial artery of the non-dominant arm after at least 5 min of quiet rest and with 1 min of recovery between measures. SBP will be defined as the average of the three pressures, and will be recorded at baseline, weekly throughout the intervention, after the 24-week training period, and at 4- and 12-weeks post-intervention.

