##### Muscle Sympathetic Nerve Activity

Muscle sympathetic nerve activity (MSNA) will be recorded from the common peroneal nerve *via* tungsten microelectrode (200 μm: 25–40 mm, impedance: 5 MX) (FHC, Bowdoin, ME) inserted percutaneously immediately posterior to the fibular head. Due to the technically difficult and time-consuming nature of MSNA, it will be assessed in a subset of subjects in the CHART study (*n* = 10/group). Subjects selected to complete MSNA testing will do so at a visit separate from Visit 1 and Visit 2 at baseline, after the 24-week intervention, and at the 12-week follow-up. Subjects will rest in a chair reclined ~45° with the right knee and foot supported by positioning pillows (VersaForm, Performance Health, Warrenville, IL). Microelectrode placement will be confirmed *via* electrical stimulation (0.02 mA, 1 Hz) as described previously (62, 63). A second microelectrode will be inserted just below the skin surface ~1.0 cm from the first to serve as a reference electrode. Electrode position in sympathetic fascicles will be confirmed by pulse synchronous bursts of activity, elicitation of afferent nerve activity by mild muscle stretch, and absence of response to light stroking of the skin or with startle response to loud noises (62). The recorded signal will be amplified (gain 2 × 10^4^), bandpass filtered (500–2.0 kHz) using a pre-amplifier (NeuroAmp Ex; ADInstruments, Colorado Springs, CO), and signals will be full-wave rectified (100 ms moving window) and sampled at 10 kHz. The resulting signal will be monitored using a computer-based data acquisition and analysis system (LabChart 8.0 software, ADInstruments, Colorado Springs, CO) and loudspeaker throughout the experiment. MSNA will be recorded for 10 min, and bursts that exceed a predetermined threshold will be marked and counted. Outcomes will include bursts/minute, bursts/100 heart beats, and mean burst area/minute.

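### Equal correlation implied between unevenly spaced visits can make the standard error of change from baseline too small, so the nominal 5% tests may run modestly high

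*Protocol article*

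**What the plan says.** One model serves every hypothesis. The protocol article, Statistical Analysis, calls it "A standard repeated measures (with the number of time points depending on outcome) mixed model analysis of variance". Dependence within a person is handled in one sentence: "Subject specific random effects will be used to account for the repeated measures on an individual". Estimation follows: "Inferences will be based on available data using maximum likelihood, which accommodates data missing at random". On the contrast: "comparisons between arms will be based on average change from baseline vs. average at endpoint". On the level: "Unless otherwise mentioned, tests will be two-sided and conducted at the 5% significance level".

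The only correlation given is at a short interval: "the correlations between baseline and 6-week SBP and plasma norepinephrine in our preliminary data were ~0.60 or larger". No correlation is given at 24 weeks or between any other pair of visits.

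Study Design sets four assessments: baseline, post-intervention, and 4 and 12 weeks later. Study Location and Timeline puts them at about weeks 0, 25, 29 and 37. The primary-outcome section adds that casual SBP "will be recorded at baseline, weekly throughout the intervention, after the 24-week training period, and at 4- and 12-weeks post-intervention". Of muscle sympathetic nerve activity (MSNA) the article says "it will be assessed in a subset of subjects in the CHART study", with 10 per group and three time points.

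**The concern.** A random subject intercept with independent residuals makes every pair of visits equally correlated. Here baseline stands alone, 25 weeks or more from the other three visits, which lie within 12 weeks of each other. If readings close in time are more alike than readings far apart, the pooled within-subject variance is pulled down by the close pairs. It then understates the variance of the one change that matters most, baseline to week 25. It understates baseline to 12-week follow-up even more, and that contrast bears on the persistence hypothesis.

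Confidence intervals for the between-arm change would then be too narrow, and the stated 5% level would be exceeded. Comparisons between neighbouring late visits would err the other way.

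Maximum likelihood also divides by the number of subjects without allowing for the estimated means. That is trivial with 90 people but not with 20.

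**Working it through.** **Plan's own figure.** Sample Size Calculation and Power states over 80% power with 45 completers per arm at effect size 0.63. Normal approximation: 0.63 × √(45/2) = 2.988; 2.988 − 1.960 = 1.028; power = Φ(1.028) = 84.8% (84.0% with the t distribution). The statement holds. For type I error the plan gives only the nominal 5%.

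**Inputs from the article.** n = 45 per arm (N = 90); two-sided 5%; visits at weeks 0, 25, 29, 37; MSNA 10 per group at 3 visits; correlation about 0.60 or larger at 6 weeks.

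**Assumed.** Random intercept only, independent residuals, Wald z, complete data, and correlation c₀·exp(−lag/τ).

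**Formulas.** Let ρ̄ be the mean correlation over all visit pairs and ρ the correlation between baseline and the visit tested.
- True variance of the between-arm difference in change: 4σ²(1 − ρ)/n.
- Variance the model reports, on average: 4σ²(1 − ρ̄)/n × (N − 2)/N. The last factor is the maximum-likelihood effect, 88/90 = 0.978.
- Size ≈ 2[1 − Φ(1.96 √r)], with r the reported variance over the true variance.

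**Worked case, c₀ = 0.8, τ = 87 weeks.** The lags 25, 29, 37, 4, 12 and 8 weeks give correlations 0.600, 0.573, 0.523, 0.764, 0.697 and 0.730, so ρ̄ = 3.887/6 = 0.648.
- Week 25, covariance alone: r = 0.352/0.400 = 0.881; 1.96 × 0.939 = 1.840; size 6.6%.
- With the factor 0.978: r = 0.861; size 6.9%.

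**Four visits, 45 per arm** (each cell: covariance alone / with maximum likelihood)

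| Correlation at 6 wk → 25 wk | ρ̄ | Week 25 | 12-week follow-up |
|---|---|---|---|
| 0.60 at all lags | 0.600 | 5.0% / 5.3% | 5.0% / 5.3% |
| 0.60 → 0.55 | 0.566 | 5.4% / 5.7% | 6.2% / 6.5% |
| 0.65 → 0.60 | 0.616 | 5.5% / 5.7% | 6.4% / 6.7% |
| 0.60 → 0.50 | 0.532 | 5.8% / 6.1% | 7.2% / 7.5% |
| 0.75 → 0.60 (c₀ 0.8, τ 87) | 0.648 | 6.6% / 6.9% | 9.2% / 9.6% |
| 0.75 → 0.50 (c₀ 0.85, τ 47) | 0.583 | 7.4% / 7.7% | 10.6% / 11.0% |

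Simulation with 20,000 trials per row agrees within about 0.2 points. In round terms, any decay in this table gives 5.5% to 7.5% at week 25 and 6.5% to 11% at the 12-week follow-up. The week-25 standard error is about 2% to 9% too small from the covariance alone. A harsher pattern, pure exponential decay with no measurement-error component, gives up to 8.8% at week 25 with four visits. A test on change scores stays near 5% throughout (4.5% to 5.9% in simulation).

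**If training-visit readings entered.** With about 17 readings (weeks 0 to 4, every second week to 22, then 25, 29 and 37), the last two patterns give ρ̄ = 0.697 and 0.663. The week-25 size is then 9.2% and 11.2%.

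**MSNA, equal correlation assumed true.** Degrees of freedom are (20 − 2)(3 − 1) = 36; the maximum-likelihood divisor is 20 × 2 = 40; √(36/40) = 0.949.
- Wald z: P(|t₃₆| > 1.96 × 0.949 = 1.859) = 7.1%.
- t reference on 36 df: P(|t₃₆| > 2.028 × 0.949 = 1.924) = 6.2%.
- REML with t: 5.0%.

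**The case against.** **The article does not say intercept only.** Random effects is in the plural, and random slopes, a residual structure or small-sample degrees of freedom would all fit the wording. An unseen analysis plan may specify them. This stands in part: the size of the problem depends on the ordinary reading. Adding a random slope lowers the two steeper four-visit cases to about 6.2% to 6.7% but does not remove the excess. Moreover, the article positively names subject random effects as the device and maximum likelihood as the method, so the change below replaces stated text and does not merely fill a gap.

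**The decay is assumed.** This stands. The two steepest rows start from about 0.75 at 6 weeks. Starting from the documented 0.60, the week-25 figure is only about 5.7% to 6.1%.

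**A reader might infer that the weekly SBP readings are in the primary model.** The documents do not support that. Study Design names four time points. Table 2 lists casual BP only at baseline, post and follow-up visits, with vitals alone during training. Training-visit BP is taken by the unblinded technician, whereas outcome assessors are blinded. The number of time points varies by outcome in any case: sleep testing has two, the cognitive battery and MSNA three. Still, the primary-outcome section does list weekly recordings, and nothing expressly excludes them.

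**A reader might blame maximum likelihood.** For SBP it adds only about 0.3 points; the covariance assumption does the rest.

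**A large effect would not be affected.** If the preliminary SBP effect size of 2.50 were repeated, a standard error a few per cent too small would not alter the conclusion. That is fair for casual SBP, less so for 24-h SBP, whose preliminary effect size was 0.63.

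**Conclusion.** The point holds conditionally. Under a random-intercept reading, and if correlation declines with time, the planned test of change from baseline is mildly anti-conservative with four visits: about 5.5% to 7.5% at week 25 and 6.5% to 11% at the 12-week follow-up. If correlation is equal at all lags, size is about 5.3% and there is nothing to correct for SBP. The week-25 figure reaches about 9% to 11% only if training-visit readings were also modelled.

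It would be wrong to conclude that the 5% tests do run at 7% to 11%. That needs an intercept-only model, a decay pattern and extra readings, none of which the article fixes.

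For MSNA, maximum likelihood with a Wald z test gives about 7% even when equal correlation is true, and about 6% with a t reference. MSNA is one of the other outcomes and appears in none of the stated hypotheses, so this carries little weight for the trial's main conclusions.

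The change is still worth making. The same model serves the primary endpoint, and its error rate need not depend on an equal-correlation assumption that the design gives reason to doubt.

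**What to change.** For outcomes measured at the four assessment visits, specify a repeated-measures mixed model with arm-by-visit means and an unstructured within-subject covariance, fitted by REML with Kenward-Roger degrees of freedom. This remains likelihood-based, so the missing-at-random rationale is kept. Four visits need 10 covariance parameters (4 × 5/2), which 90 completers support easily. Use the same REML and degrees-of-freedom rule for MSNA, with three visits and 6 parameters (3 × 4/2).

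State that training-visit BP readings stay out of the primary model and are reported descriptively. Name in advance a fallback covariance in case the model does not converge.

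The cost is a change of wording, slightly wider confidence intervals and the need to define that fallback. No new data are required.
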